### Ethical issues and trial registration

The pilot trial will be conducted in accordance with Health Canada’s Good Clinical Practice guidelines [45] in accordance with the current Declaration of Helsinki and the Tri-Council Policy Statement: Ethical Conduct for Research Involving Humans [46]. All patients will be informed that they can withdraw from the study at any time. Patients who agree to participate to the study will provide a written informed consent. The study protocol and informed consent forms have been approved by the Ottawa Health Science Network Research Ethics Board. The trial is registered at the US National Institutes of Health (ClinicalTrials.gov) # NCT02084771.

### Statistical analyses

#### Baseline analyses

Baseline characteristics of patients in the two treatment arms will be assessed by calculation of frequency distributions and univariate descriptive statistics including measures of central tendency and dispersion.

#### Feasibility outcomes

For the recruitment rate, we will calculate the proportion (and 95% confidence interval) of all CKD stage 4 patients who are randomized into the trial among those who undergo a contrast-enhanced CT scan of the abdomen or chest. In addition, we will calculate the proportion of patients that were eligible but who declined consent, those who were eligible but were not approached. For the feasibility outcome of adherence, we will calculate the proportion of patients who will complete the fluid ingestion in both arms out of all those recruited. The follow- up will be measured by calculating the proportion of participant recruited who complete the follow-up (the proportion of patients who will undergo repeat measures of creatinine at 48 hours and 28 days among those recruited). Proportion of patients who will be adherent and those who will complete the follow-up will be compared between the arms with an unadjusted chi-square, or with Fisher’s exact test if the cell sizes are small.

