**Methods:**

Our study is a pilot, single-centre parallel randomized controlled trial. To be included, participants must be at stage 4 of chronic kidney disease as defined by a glomerular filtration rate <30 mL/min/1.73 m^2^, aged greater than 18 years and to undergo an outpatient contrast-enhanced computer tomography of the chest or abdomen. A total 50 patients will be randomised to receive either oral salt and water or intravenous isotonic saline. The primary outcome is feasibility, including estimates of recruitment rate, adherence to intervention and completeness of follow-up to assist in planning the definitive trial. The secondary outcome is safety and includes adverse events with oral salt and water loading as compared to intravenous isotonic saline.

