### Participants

Participants will be identified within the medical imaging department. Eligible patients are outpatients who are scheduled for a contrast-enhanced CT scan of the chest or abdomen. We plan to enrol 50 patients in this pilot trial. Since this is a pilot trial to assess feasibility, we did not carry out a formal sample size calculation. The rate of recruitment in this trial will allow us to plan the recruitment strategy and duration of the definitive trial. For the large definitive trial (planned as a non-inferiority trial) our preliminary estimates for sample size suggests we need to recruit 1030 patients.

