**Study flow chart.**

### Randomization and allocation concealment

Patients will be randomized to receive either oral salt and water or intravenous saline. The randomization process will consist of a computer generated random listing of the treatment allocations in permuted blocks of varying size. For example, given a block size of 4 patients recruited, there will be 2 allocations to oral salt and water arm and 2 to the intravenous saline arm. The system will have backup in the form of an independent statistician who will be informed and able to issue the treatment allocation in the event of a system malfunction/shutdown.

The randomization will be performed independently by a statistician after eligibility is documented by the Principal Investigator/Co-Investigators based on inclusion/exclusion criteria and after the patient signs the informed consent. From the computer random listing a code will be assigned to each new subject. This randomization code is a participant unique identifier (ID) and corresponds to the study treatment that will be given to the patient. Patient will be considered randomized as soon as the randomization code is given. All patients who are allocated a randomization code (i.e., study treatment number) will be irrevocably in the study and they will be followed until the end of study, loss to follow-up or death whichever comes first. The randomization codes corresponding to the participant ID will be printed and put in numbered sealed envelopes. On the day of the CT scan, these envelopes will be delivered to the imaging room to be opened by the Principal Investigator who will administer the trial treatment.

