#### Safety

For the safety outcome, we will calculate the frequency of overall adverse events that will occur in each trial arm and we will compare them using an unadjusted chi-square test or Fisher’s exact test. Univariate descriptive statistics including measures of central tendency and dispersion will be used to report the frequency of adverse events. This outcome will be underpowered to draw any definite conclusions, but will be conducted to help us design the definitive trial.

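### Adherence and follow-up are compared by significance tests in arms of about 25 with no interval or power caveat, and the single overall adverse-event test can hide route-specific differences

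*Protocol article*

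**What the plan says.** The Abstract (Methods) and the Outcomes section make feasibility the primary outcome, with recruitment, adherence to the intervention and completeness of follow-up as its components. Safety is secondary.

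On size, the Abstract says "A total 50 patients will be randomised to receive either oral salt and water or intravenous isotonic saline". The Participants section adds "Since this is a pilot trial to assess feasibility, we did not carry out a formal sample size calculation". The block example under Randomization and allocation concealment ("given a block size of 4 patients recruited, there will be 2 allocations to oral salt and water arm and 2 to the intravenous saline") implies equal allocation, hence about 25 per arm.

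On analysis, the Feasibility outcomes section treats the three components differently. For recruitment: "For the recruitment rate, we will calculate the proportion (and 95% confidence interval) of all CKD stage 4 patients who are randomized into the trial". For adherence and follow-up it plans the proportions and then a between-arm test: "Proportion of patients who will be adherent and those who will complete the follow-up will be compared between the arms with an unadjusted chi-square", with Fisher's exact test as the fallback when cells are small. No interval is named for either, and nothing is said about the power of these tests.

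On safety: "we will calculate the frequency of overall adverse events that will occur in each trial arm and we will compare them", again by chi-square or Fisher's test. Descriptive statistics are added, with this caveat: "This outcome will be underpowered to draw any definite conclusions, but will be conducted to help us design the definitive trial". The Outcomes section expects gastrointestinal symptoms from the oral regimen and access-site symptoms from the intravenous one, recorded on a questionnaire that lists them.

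The Discussion says adherence and follow-up will be used to refine the protocol and adjust the sample size of the larger trial. Frequency and severity of adverse events will inform the judgement on whether that trial is worth its risks.

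**The concern.** Adjusting a sample size for non-adherence or loss to follow-up requires an estimate of each proportion and a range around it. A p-value for the difference between arms supplies neither. It also answers a question that the pilot was not sized to answer, so a large p-value says little about whether the arms are alike.

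The stake is practical. If patients tolerate one regimen clearly less well than the other, the definitive trial needs to allow for it, particularly as the Participants section plans it as a non-inferiority trial. A non-significant test at 25 per arm would not rule that out, and without an interval beside it a reader may not see how little it rules out.

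The safety comparison has a second problem, separate from power. A single overall frequency sets nausea in one arm against venipuncture pain in the other. If each route produces its own symptoms at similar rates, the overall comparison shows nothing, however different the arms are.

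**Working it through.** The protocol states no power, significance level or expected rate for these comparisons, so there is no figure of its own to reproduce. What follows shows what the planned tests can do.

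**Inputs**
- From the protocol: 50 patients, equal allocation implied by the block example, so n = 50/2 = 25 per arm; chi-square, or Fisher if cells are small.
- Assumed: two-sided 5% level; uncorrected chi-square; small cells meaning an expected count below 5; all rates and counts below.

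**Power.** For true rates p1 and p2, sum over all pairs (a, b) from 0 to 25:

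Power = Σ Bin(a; 25, p1) × Bin(b; 25, p2) × 1[p-value(a, b) ≤ 0.05]

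The p-value is Fisher's when the smaller expected count, min(a + b, 50 − a − b)/2, is below 5, and chi-square otherwise.

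| True rates | Fisher throughout | Chi-square throughout | Planned rule |
|---|---|---|---|
| 95% v 80% | 20% | 38% | 22% |
| 90% v 70% | 30% | 45% | 41% |
| 95% v 60% | 82% | 91% | 88% |

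Under the planned rule, power reaches about 82% at 95% v 63%, a gap of 32 points.

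**One illustrative result.** Adherence 24/25 v 20/25. The 6 non-adherent patients give an expected count of 6/2 = 3 per arm, so Fisher applies: p = 0.19.
- Difference: 0.96 − 0.80 = 0.16.
- Wilson 95% limits: 0.805 to 0.993 for 24/25, and 0.609 to 0.911 for 20/25.
- Newcombe lower limit: 0.16 − √[(0.96 − 0.805)² + (0.911 − 0.80)²] = 0.16 − 0.191 = −0.03.
- Newcombe upper limit: 0.16 + √[(0.993 − 0.96)² + (0.80 − 0.609)²] = 0.16 + 0.194 = 0.35.

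The interval, −3 to 35 points, shows what the p-value does not: the data fit anything from a small advantage to a large deficit. Even identical arms, 22/25 v 22/25 with p = 1.00, leave an interval of −20 to +20 points.

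**Pooling of adverse events.** Assume gastrointestinal symptoms in 40% of the oral and 5% of the intravenous arm, access-site symptoms in 5% and 40%, and independence between the two kinds.
- Any event, oral: 1 − (1 − 0.40)(1 − 0.05) = 1 − 0.57 = 43%.
- Any event, intravenous: 1 − (1 − 0.05)(1 − 0.40) = 43%.

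The overall test then has no difference to find: 11/25 v 11/25 gives p = 1.00. The gastrointestinal contrast alone, 10/25 v 1/25, gives Fisher p = 0.005.

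**The case against.** The strongest reply is that the protocol never draws the wrong conclusion. A reader might infer from the planned tests that non-significant results will be presented as comparable adherence, follow-up and safety. The document does not support that: it has no rule treating p > 0.05 as similarity, no go/no-go decision tied to a p-value and no equivalence claim. The misreading is a risk, not a stated plan.

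On safety the reply goes further. The protocol says outright that the outcome has too little power for firm conclusions. It adds descriptive reporting, collects symptoms individually and sends serious events to an independent board. The overall count is therefore not the whole safety assessment. A reader might also infer that the test breaks independence because one patient can report several symptoms. That holds only if events are the unit; the text does not say so, and a count of patients with an event is the more natural reading.

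A further temptation is to quote Fisher's power alone, or to say that the tests will almost never be significant. Chi-square is named first, and at 90% v 70% the planned rule gives about 41%, so both overstate the matter.

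Finally, intervals can be derived from reported counts, and a statistical analysis plan, not available here, may specify them along with tables by symptom. That is fair, but the point does not rest on missing detail. The article itself names an interval for one primary component and a test for the other two, gives the power caveat for safety only, and chooses an overall frequency as the safety comparison. The caveat does not cure the pooling, which concerns what is being compared and not how many patients there are.

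**Conclusion.** The point stands as a weakness of analysis and interpretation, not a numerical error. Two of the three primary feasibility components are compared by tests that have about 22% to 41% power for gaps of 15 to 20 points, with no interval or caveat beside them, although the results are meant for planning. These figures rest on 25 per arm, a two-sided 5% level, the assumed rates, and an expected count below 5 as the trigger for Fisher's test.

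For safety the conclusion is narrower. Low power is already acknowledged; what remains is that the overall comparison can conceal opposite differences by route. The 43% v 43% example shows that this is possible under assumed rates. It does not predict that it will happen.

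The change is worth making because it is cheap and gives the definitive trial the ranges it needs.

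**What to change.** **Feasibility outcomes section.** Replace the between-arm tests with estimation:
- Report adherence, completion of the 48-hour creatinine and completion of the day-28 creatinine as three separate proportions, per arm and overall, each with a Wilson or exact 95% confidence interval. Separate time points also match the Data collection section, which wants follow-up known at each one.
- Give each arm difference with a Newcombe 95% confidence interval.
- Make no significance claim, and extend to these outcomes the power caveat now given for safety.

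**Safety section.** In place of the single overall test, report the number of patients with at least one event in each category already on the questionnaire (gastrointestinal, access-site), and with serious events, per arm, with the risk difference and its 95% confidence interval. Naming patients as the unit also removes the ambiguity in the word frequency.

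**Cost.** Changes to the analysis wording only; no new data, visits or patients. The p-values are dropped or demoted.

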#### Safety

For the safety outcome, we will calculate the frequency of overall adverse events that will occur in each trial arm and we will compare them using an unadjusted chi-square test or Fisher’s exact test. Univariate descriptive statistics including measures of central tendency and dispersion will be used to report the frequency of adverse events. This outcome will be underpowered to draw any definite conclusions, but will be conducted to help us design the definitive trial.

### Study management and patient safety

A trial management group involving the Principal investigator (SH), two Co-investigators (AA, GK) and study coordinator (EM) will review, implement and supervise all aspects of this pilot trial. The Data Management Services group of the Ottawa Hospital Research Institute will generate the random listing. Under the guidance of the Principal investigator and the study coordinator, the coordinating centre located at the Clinical Epidemiology Program of the Ottawa Hospital Research Institute will be responsible for receiving, processing, editing storing and analyzing all data.

A DSMB will have responsibility for the monitoring of adverse events throughout the study and will work independently from the trial. The DSMB will consist of three individuals with expertise in clinical trials, biostatistics, nephrology and radiology. All serious adverse events will be reported to and reviewed by the DSMB. The DSMB will recommend termination or continuation of the study in the event of an unexpected adverse event rate.

All investigational products supplies in the study will be stored in a secure, safe place, under the responsibility of the Investigator.

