### Data collection

At baseline, participant demographic information (including ethnicity, sex, month and year of birth), CT scan characteristics, medical history and medication use will be recorded. On the day of the CT scan, before oral or IV fluids are given, a SCr will be measured that will be considered as the baseline value. A subsequent SCr level will be measured at 48 hours post-CT. If the SCr at 48 hours has increased by ≥25% or ≥44 μmol above the baseline value, the SCr will be repeated every 48 hours until it returns to within 25% of baseline or < 44 μmol above baseline or the patient needs to initiate acute dialysis. If the SCr has not returned to within 25% of baseline or < 44 μmol above baseline by day 14 post-CT, the SCr will be measured again on day 21. All participants (regardless of whether they developed AKI) will have SCr repeated on day 28 post- CT (Figure 2). The SCr will be measured in the biochemistry lab at the Ottawa Hospital. The repeat creatinine measurements, though underpowered for any assessment of efficacy, will allow us to ascertain the proportion of patients who follow-up at each time point, which will be critical for our larger definitive trial. The study timeline is shown in Table 1.

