**Repeat creatinine test schedule.**

**Table 1 Tab1:** **Study timeline**

	**Study period**							
	**Enrolment**	**Allocation**	**Post allocation**					**Close-out**
	**-t** _**1**_	**o**	**Day** _**1**_	**Day** _**2**_	**Day** _**3**_	**Day** _**4**_	**etc.**	**Day** _**28**_
Enrolment:								
Eligibility screen	X							
Informed consent	X							
Demographic data collection	X							
Medication use data collection	X							
serum creatinine testing	X				X			X
Allocation		X						
Interventions:								
Intravenous saline solution			X					
Oral salt water			X					
Assessments:								
Adherence to intervention			X					X
Adverse events			X					
serum creatinine testing					X			X

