### Outcomes

Feasibility of conducting the definitive trial is the primary outcome for this pilot study. It will be determined by the proportion of patients who will 1) consent to enrolment in the study (recruitment rate), 2) complete the fluid ingestion at dose required in both arms (adherence to intervention), and 3) complete repeat measures of creatinine at 48 hours and 28 days (follow-up). Additionally, we will identify logistical issues related to screening, protocol implementation, randomization implementation strategy, time, and budget problems that can occur during the definitive trial.

The secondary outcome for this pilot trial is safety. It will be assessed by adverse effects occurring after receiving the trial treatment. Adverse effects that may occur because of the ingestion of water and salt include: nausea or gastrointestinal symptoms. Symptoms that may occur because of the saline solution or the technique of administration include discomfort with the venipuncture at the site of injection such as skin irritation and pain, hemorrhage, hematoma, thrombosis, phlebitis. All adverse events effects will be assessed by patients self-reported symptoms using a questionnaire with these symptoms listed and will be recorded in a Case Report Form at the end of the volume expansion protocol.

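### The adverse event capture rule ends with volume expansion, so a non-serious creatinine rise at 48 hours enters neither the by-arm safety comparison nor the rate the DSMB acts on

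*Protocol article*

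**What the plan says.** All references are to the protocol article.

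- **Outcomes.** Safety is the secondary outcome. The effects named are nausea and gastrointestinal symptoms for the oral arm, and venipuncture or infusion-site problems for the intravenous arm. Then: "All adverse events effects will be assessed by patients self-reported symptoms using a questionnaire with these symptoms listed", and the results "will be recorded in a Case Report Form at the end of the volume expansion protocol".
- **Table 1, Study timeline.** The row "Adverse events" is marked on Day 1 only.
- **Data collection.** Creatinine is measured before fluids on the CT day and first repeated at 48 hours. "If the SCr at 48 hours has increased by ≥25% or ≥44 μmol above the baseline value, the SCr will be repeated every 48 hours". The stated purpose of the repeat measurements is to learn what proportion of patients attend at each time point.
- **Statistical analyses, Safety.** "we will calculate the frequency of overall adverse events that will occur in each trial arm". Creatinine and acute kidney injury (AKI) are not mentioned.
- **Study management and patient safety.** "A DSMB will have responsibility for the monitoring of adverse events throughout the study", and "All serious adverse events will be reported to and reviewed by the DSMB". The action attached is: "The DSMB will recommend termination or continuation of the study in the event of an unexpected adverse event rate".

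**The concern.** Both regimens exist to prevent AKI, and every participant has a GFR below 30. If oral loading is inferior, AKI is the main harm to expect. Under the stated capture rule, the non-serious part of the adverse event rate consists of same-day gastrointestinal and cannula-site symptoms. An imbalance in creatinine rises would be visible to the DSMB only through cases that become serious.

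The same record is used later. The Discussion says that the frequency and severity of adverse events will inform whether a larger trial is justified. AKI itself is mentioned there only as the efficacy outcome of the definitive trial.

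**Working it through.** **1. Timing and content of the capture rule**

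The article gives no figure to reproduce here, so the first step compares its statements.

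| Item | Oral arm | Intravenous arm | Where stated |
|---|---|---|---|
| Volume expansion ends | 2 h after CT | 6 h after CT | Trial intervention and dosing; The intravenous saline arm |
| Adverse events recorded | at that point | at that point | Outcomes |
| Symptoms named | gastrointestinal | venipuncture or infusion site | Outcomes |
| First repeat creatinine | 48 h | 48 h | Data collection |

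A creatinine rise falls outside the rule twice. It is measured 42 to 46 hours after the record is made (48 − 6 and 48 − 2), and a patient cannot self-report it. The only consequence attached to a rise is retesting. The only explicit route to the DSMB that could carry it is the one for serious events.

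**2. How many events are at issue (illustration)**

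Inputs:
- 25 patients per arm (50 planned, equal allocation).
- Pooled odds ratio 1.2, 95% CI 0.46 to 3.10, from the Background; all six trials used arterial contrast.
- Assumed, because the article gives neither: control risk p of 5, 10 or 15%, and non-serious share s of 50 to 90%.

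Oral-arm risk: q = OR × p/(1−p) ÷ [1 + OR × p/(1−p)].

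| OR | q at p = 5 / 10 / 15% |
|---|---|
| 0.46 | 0.024 / 0.049 / 0.075 |
| 1.2 | 0.059 / 0.118 / 0.175 |
| 3.10 | 0.140 / 0.256 / 0.354 |

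Expected non-serious rises = 25 × risk × s, from the lowest corner (p = 5%, s = 0.5) to the highest (p = 15%, s = 0.9):
- Intravenous arm: 25 × 0.05 × 0.5 = 0.6 to 25 × 0.15 × 0.9 = 3.4.
- Oral arm: 0.3 to 1.7 at OR 0.46; 0.7 to 3.9 at OR 1.2; 1.8 to 8.0 at OR 3.10.

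**3. What the serious-event route alone would miss**

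Chance that no oral-arm case reaches the DSMB = (1 − q(1−s))^25. At OR 3.10, for p = 5 / 10 / 15%:
- s = 0.5: 16 / 3 / 1%.
- s = 0.9: 70 / 52 / 41%.

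**4. What a by-arm listing would show**

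Chance of an oral excess of 3 or more at full enrolment, from two independent Binomial(25) counts, for p = 5 / 10 / 15%:
- Equal arms: 5 / 12 / 16%.
- OR 1.2: 8 / 17 / 23%.
- OR 3.10: 44 / 70 / 81%.

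If the listing is looked at after each pair of patients (one per arm), the equal-arm chance of ever seeing such an excess rises to about 6 / 16 / 24%. The excess of 3 is only a descriptive yardstick.

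**5. The retest threshold**

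The two limits meet at a baseline of 44/0.25 = 176 μmol. Above that, 44 μmol is a rise of less than 25%. At assumed baselines of 200, 300 and 400 μmol it is 22%, 15% and 11%.

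**The case against.** A reader might infer that the Outcomes and Study management sections contradict each other. They do not. The phrase about the whole study qualifies the DSMB's monitoring and can mean the calendar life of the trial. A reader might also infer that the DSMB cannot see AKI, or that affected patients go unwatched. Neither is supported: AKI leading to dialysis or hospitalization would arrive as a serious adverse event, and any patient over the threshold is retested.

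Four further objections deserve weight.

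- **The questionnaire sentence may describe only the tolerability instrument.** It follows directly on the symptom lists, and serious events plainly come from elsewhere. This is a fair reading. But the sentence speaks of all adverse events, and the article states no other source for the non-serious events that the Safety analysis counts.
- **What a DSMB is shown is usually charter content.** This stands. A missing listing would not be a finding by itself, and an unseen charter may provide one. The point rests on the capture rule that the article does state.
- **Table 1 is weak evidence.** This also stands. Its Day 1 column has no creatinine mark although Data collection requires one on the CT day, so the table is incomplete.
- **The stakes are modest and the numbers assumed.** The pilot has 50 patients, and the article calls its creatinine data underpowered for efficacy. It reports no clear evidence favouring the intravenous route and excludes patients whose physician ordered intravenous saline. The trial management group could consult the creatinine data in any case. The chance in step 3 runs from 1% to 70% and uses the upper confidence limit from arterial-contrast trials. At OR 1.2 a listing would hardly differ from equal arms. All this limits the importance of the point without removing it.

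**Conclusion.** The point holds in a limited form and is worth considering, with medium confidence. Followed as written, the capture rule leaves the harm that both regimens are meant to prevent out of the by-arm safety comparison and out of the DSMB's adverse event rate, unless a case becomes serious. The gap concerns aggregate review by arm, not the care of individual patients.

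Its size cannot be fixed from the article, which gives neither the AKI risk nor the share of rises that stay non-serious. If AKI is often serious, little is lost. If it seldom is, and oral loading is clearly worse, the DSMB could well see no oral-arm case at all.

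**What to change.** In Outcomes, keep the questionnaire as the tolerability measure and add text to this effect: *a creatinine rise at 48 hours that meets the retest threshold in Data collection (25% or 44 μmol above baseline), or any start of acute dialysis, is recorded as a safety event; these events are reported separately by arm, descriptively, and are included with their values and retests in what the DSMB reviews.* Leave the serious adverse event line and the open DSMB trigger as they are. Add no test and no numeric trigger.

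The cost is a sentence and a short listing to an existing committee, using results already collected. There are two downsides:

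- **Chance imbalance may prompt an unneeded review.** The equal-arm figures in step 4 show how often, and review during accrual makes it more frequent than a single look at the end.
- **Some listed rises may be ordinary fluctuation.** Above 176 μmol the 44 μmol limit is the looser of the two. Showing the actual values and retests lets the DSMB judge, and its stated expertise includes nephrology.
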